#### Primary and secondary outcomes

Table 1 presents the primary and secondary outcomes. The outcomes will be assessed utilizing the electronic survey at baseline and after 6 months.

**Table 1. table1-02601060251332358:** Primary and secondary outcomes.

Primary outcome variables	Measurement
Depressive symptoms	CES-D (Radloff, 1977)
Work ability	Current work ability compared with the lifetime best (Tuomi et al., 2007) Three-level work ability indicator (Gould et al., 2015)
Secondary outcome variables	Measurement
Sick leave days related to depressive symptoms	Structured question about sick leave days during the past 6 months
Quality of life	WHO8-EUROHIS (WHO, Power, 2003)
Dietary habits	Food Frequency Questionnaire (Männistö et al., 1996) Healthy Diet Index (HDI; Lindström et al., 2021) Three-day food records Three Factor Eating Questionnaire – 18 (TFEQ-18; Karlsson et al., 2000)
Intervention adherence	Goal Attainment Scaling (GAS; Kiresuk and Sherman, 1968) Level of participation
Intervention acceptability	The Theoretical Framework for Acceptability (TFA; Sekhon et al., 2022)

CES-D: Center for Epidemiological Studies – Depression; TFEQ-18: Three Factor Eating Questionnaire – 18; WHO: World Health Organization.

##### Primary outcome: Change in depressive symptoms

The primary outcome is the change in depressive symptoms measured with the CES-D scale (Radloff, 1977). This scale is commonly used to assess depressive symptoms in the general population. Its 20 items enquire about various symptoms of depression experienced over the past week, such as feelings of sadness, loss of interest and sleep disturbances. Each item is scored on a scale from 0 to 3, indicating the frequency of experiencing that symptom (0 = Rarely or none of the time, 1 = Some or a little of the time, 2 = Occasionally or a moderate amount of time, 3 = Most or all the time). Points from questions 4, 8, 12 and 16 are reverse-scored. The total CES-D score is the sum of the responses to all items, between 0 and 60, with a higher score reflecting more severe depressive symptoms. Typically, a cut-off score of 16 or more points indicates significant depressive symptoms.

##### Primary outcome: Change in work ability

We will measure work ability with two indicators. The first one is ‘Current work ability compared with the lifetime best’ assessed with one question: ‘Assuming that the best working capacity you have ever had would score 10 on a scale of 0 to 10, how would you score your working capacity at present? A score of 0 would mean that you are completely unable to work at present’ (Tuomi et al., 2007).

The second is a three-level work ability indicator based on one question: ‘Regardless of whether you are employed or not, please estimate your current work ability. Are you: 1) completely fit for work, 2) partially unable to work and 3) completely unable to work’ (Gould et al., 2015). The first indicator has been demonstrated to be a reliable and practical alternative to the longer version of the Work Ability Index, and the second indicator has predicted the risk of retiring on disability pension (Gould et al., 2015).

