The primary aim of the Mind Nutrition randomized controlled trial is to examine the effectiveness of nutrition counselling on depressive symptoms and work ability among nurses and social services professionals working in the mental health and substance abuse fields. The secondary aims are to examine the effectiveness of depression-related sick leave days, quality of life and dietary habits. This article is a detailed description of the study protocol. This is the first study that provides evidence on the effects of nutritional counselling on depressive symptoms, work absenteeism and work ability among mental health professionals.

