#### Sample size calculation

We calculated the sample size based on the expected change in depressive symptoms, measured with the CES-D scale (Radloff, 1977). We expect depressive symptoms to decrease in the intervention group from 14 to 9.9 points (Katsuta et al., 2021; Konttinen et al., 2010; Mondal et al., 2022) and assume that depressive symptoms will not change in the control group. The calculation is based on an estimated power of 0.8 with an expected dropout rate of 25%. The calculated sample size was 125, meaning 62 or 63 participants per group (ß = 0.2, a 0.05).

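### Two domains with three measures are labelled primary, but the only alpha and power cover CES-D alone and the text conflicts on which outcome leads

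*Protocol article*

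**What the plan says.** The protocol article describes its primary outcome in two ways.

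- **One primary outcome.** The section on depressive symptoms states: "The primary outcome is the change in depressive symptoms measured with the CES-D scale". The sample size section rests on the same variable: "We calculated the sample size based on the expected change in depressive symptoms, measured with the CES-D scale". It gives the only error rates in the article: "The calculated sample size was 125, meaning 62 or 63 participants per group (ß = 0.2, a 0.05".
- **Two primary domains, three measures.** The Introduction sets the primary aim as to "examine the effectiveness of nutrition counselling on depressive symptoms and work ability". Table 1 lists both domains as primary. A section headed as a primary outcome covers work ability and says: "We will measure work ability with two indicators". These are a 0–10 score against lifetime best and a three-level self-rating.

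The Statistical analyses section assigns repeated-measures analysis of variance to depressive symptoms and ordinal mixed models to work ability, so the two domains are tested separately. It refers to the main outcomes in the plural. It does not combine the two work-ability indicators, rank them, or place them in order with CES-D.

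**The concern.** Which outcome is primary, and what result makes the trial positive, has to be settled before the data are seen. Here one reading gives a single-primary trial to which the 0.05 and 80% apply. The other gives three primary measures, with error rates stated for only one of them.

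Two things are at stake. If any one measure could carry the trial, 0.05 would not be the chance of a false positive conclusion. If every measure had to succeed, 80% would not be the chance of a true positive conclusion, because no power is given for either work-ability item. The outcomes are self-reported in an unblinded trial, so a lead outcome chosen after the results could not be shown to be independent of them.

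**Working it through.** **Inputs (Sample size calculation section)**

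- Intervention arm: "We expect depressive symptoms to decrease in the intervention group from 14 to 9.9 points", a fall of 14 − 9.9 = 4.1.
- Control arm: "assume that depressive symptoms will not change in the control group". The between-group difference is therefore 4.1.
- Power 0.8, dropout 25%, alpha 0.05, total 125.
- Not stated: the SD, whether the test is two-sided, and the correlation between the outcomes. I assume two-sided tests and show correlations from 0 to 0.9.

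**1. The plan's own figure**

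N = 125 cannot be reproduced outright without an SD, so I solved for the SD it implies. After 25% dropout, 125 × 0.75 = 93.75, taken as 93 completers or 46.5 per arm.

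SD = difference × √(n/2) / (z₀.₉₇₅ + z₀.₈₀) = 4.1 × √(46.5/2) / (1.960 + 0.842) ≈ 7.06

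Forward check: SD 7.0 needs 46 per arm, and 92/0.75 rounds up to 123. SD 7.05 needs 47 per arm, and 94/0.75 rounds up to 126. So 125 is consistent with an SD near 7 for CES-D tested alone at the full two-sided 0.05. It leaves no allowance for sharing alpha.

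**2. Error rate if any one success counts**

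With k independent tests at 0.05, the chance of at least one false positive is 1 − 0.95^k:

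- k = 2: 1 − 0.9025 = 9.75%
- k = 3: 1 − 0.857375 = 14.3%

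For correlated tests I used simulated equicorrelated normal test statistics (4 million draws, no effect on any measure, two-sided 0.05 each):

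| Correlation | Three tests | Two tests |
|---|---|---|
| 0 | 14.3% | 9.7% |
| 0.3 | 13.6% | 9.5% |
| 0.5 | 12.5% | 9.1% |
| 0.7 | 10.9% | 8.4% |
| 0.8 | 9.8% | 7.8% |
| 0.9 | 8.4% | 7.0% |

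The simulated 9.7% in the first row is the exact 9.75%. A more realistic pattern for three tests has correlation 0.4–0.5 between CES-D and each work-ability item and 0.7 between the two items. It gives 11.9–12.3%.

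**3. If all must succeed**

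Type I error is then at most 5%. Power cannot exceed that of the weakest test, so it is at most the 80% for CES-D. It equals that only if work ability always succeeds whenever CES-D does. The article has no figures from which to compute it.

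**4. What a later split of alpha would cost**

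This uses the implied SD of 7.06 and 47 completers per arm.

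| CES-D alpha | Power | Completers per arm for 80% | Randomized (÷ 0.75) |
|---|---|---|---|
| 0.05 | 80% | 47 | 126 |
| 0.025 (two domains) | 72% | 57 | 152 |
| 0.0167 (three measures) | 66% | 63 | 168 |

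The 126 against the plan's 125 is rounding up to whole participants per arm.

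**The case against.** **Silence is not an error.** An alpha allocation or decision rule is commonly left to an analysis plan, and a journal article condenses its protocol. That stands: a missing multiplicity rule would be no finding by itself. It does not cover the conflict over what is primary, which this article does set out. An unseen rule elsewhere would not remove it.

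**The singular may be innocent.** The two outcome sections have parallel headings, so the CES-D sentence may describe only the outcome named in its own heading. This is fair and weakens the contradiction. But on that reading work ability is fully primary, and the stated alpha and power then cover one primary measure out of three.

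**A reader might infer that the trial's false positive rate is 11–14%.** The article does not support this as an unconditional figure. It never says that any one success is enough, and the Statistical analyses section sets no test level. The aim joins the domains with a conjunction, which would fit a rule that both must succeed. Table 1 names two outcome variables, not three. Independence is implausible for two questions about the same construct put to the same person. Participants must also be work-capable, so the three-level item may vary little and its test may be conservative. The 14% is therefore near an upper value.

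**A reader might also infer that N = 125 is wrong, or that work ability must become secondary.** Neither follows. The sample size is consistent with an SD near 7. Work ability belongs to the stated primary aim, and error can be controlled without removing it.

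**Conclusion.** The point holds as an inconsistency with a conditional consequence. The article labels two domains and three measures as primary, words one of them as the primary outcome, and gives alpha and power for that one only.

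If success on any one measure at two-sided 0.05 counted, the family-wise error would be about 8–14%. For three tests it runs from 14.3% (independent) to 8.4% (correlation 0.9). For two tests it runs from 9.75% (independent) to 8.4% (correlation 0.7), and very high correlation would bring it nearer 7%. Every scenario examined exceeds 5%. If all had to succeed, type I error would be controlled and the open question would be power for work ability.

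The error-rate figures rest on the assumed success rule, the two-sided level and the correlations, none of which the article gives. The power figures under a split alpha rest in addition on the back-solved SD and are illustrative, because the article proposes no split. The inconsistency itself depends on none of these assumptions.

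**What to change.** - State that the change in CES-D is the lead primary outcome, tested first at two-sided 0.05.
- Test the 0–10 work-ability score second in a fixed sequence, at 0.05 and only if CES-D is significant.
- Report the three-level indicator as supportive.
- Bring the primary aim in the Introduction, Table 1, both primary outcome sections and the Statistical analyses section into line with this order. Work ability may remain in the primary aim as the second step.
- Say in the Sample size calculation section that N = 125 and 80% power apply to CES-D only.

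Other rules, such as requiring both domains or a Holm procedure, would also control the error rate. The fixed sequence has the advantage of matching the existing CES-D wording and calculation, so alpha stays at 0.05 and N at 125.

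The cost is a change of wording, made before results are seen. The downside is that a confirmatory claim on work ability becomes conditional on a significant CES-D result.

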##### Secondary outcome: Change in sick leave days related to depressive symptoms

We will measure depression-related sick leave days during the past 6 months. The question has the following response options: No days, 0–6 days, 7–14 days, 15–29 days, 30–49 days and 50 or more days.

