## Methods

### Participants and recruiting

#### Participants

We will recruit 125 licensed practical nurses, registered nurses, mental health nurses and social services professionals in the mental health and substance abuse fields in Pori, Satakunta Wellbeing Services County, Western Finland. We will recruit participants working in special care and primary care, outpatient departments, institutional care and rehabilitation services. The inclusion and exclusion criteria are as follows:

*Inclusion criteria:*
1.Aged 18 years or over2.Adequate Finnish language skills3.Work-capable4.Currently employed by Satakunta Wellbeing Services County for at least 6 months5.Works in the mental health and substance abuse fields6.Education is in one of the following areas: licensed practical nurse, registered nurse, mental health nurse or has a bachelor's degree in social services7.Agrees to commit to either of the groups (intervention/control) during the 6 months of intervention8.Able to give informed consent.

*Exclusion criteria:*
1.Acute mental health symptoms and inability to work2.Terminal phase disease or unstable severe chronic disease (consultation with the responsible physician)3.Employed for a shorter period than 6 months4.History of eating disorder (consultation with the responsible physician)5.A score of ≥16 on the CES-D (Center for Epidemiological Studies – Depression) scale (Radloff, 1977) and reduced work capacity (determined in consultation with the medical expert in mental health)6.Substance abuse based on the Alcohol Use Disorder Identification Test – Consumption (AUDIT-C) score (consultation with the responsible physician)

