### Statistical analyses

The results will be analysed using the IBM SPSS Statistics program and the STATA program. A statistician unrelated to the study will perform the statistical analyses. The analyses will utilize the intention-to-treat principle (Soares and Carneiro, 2002).

The normality of variables will be examined graphically and using the Shapiro–Wilk test. For the descriptive statistics, comparisons between groups will be analysed using the independent samples *t*-test for continuous, normally distributed variables, the chi-squared test for categorical variables and the Mann–Whitney *U* test for non-normally distributed variables. The difference between groups in the change in depressive symptoms, quality of life and diet quality is continuous variables and will be analysed with repeated analysis of variance. The difference between groups in the change in work ability and sick leave days related to depressive symptoms is ordinal variables and will be analysed with mixed-effect models for ordinal data. The main outcomes will be examined first overall and then stratified by gender to assess potential gender differences in intervention effectiveness.

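### As printed, the two lowest sick-leave options both include zero, so a zero-day respondent can be recorded in either of two levels that the ordinal analysis treats as distinct

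*Protocol article*

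**What the plan says.** The Protocol article, under the heading for the sick-leave outcome, sets the recall window: "We will measure depression-related sick leave days during the past 6 months". It then prints six response options: "No days, 0–6 days, 7–14 days, 15–29 days, 30–49 days and 50 or more days". Table 1 (Primary and secondary outcomes) lists sick leave as a secondary outcome with one measurement, "Structured question about sick leave days during the past 6 months", and cites no source instrument for it. The item is asked twice: "The outcomes will be assessed utilizing the electronic survey at baseline and after 6 months". Under Statistical analyses, the change in work ability and in sick leave is described as "ordinal variables and will be analysed with mixed-effect models for ordinal data".

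Nowhere does the article say which box a person with zero days should tick, print the second option as 1–6 days, or combine the two lowest levels. It gives no expected distribution of sick-leave days.

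**The concern.** Response categories for an ordinal outcome should be mutually exclusive. Here a person with no depression-related leave gives a literally true answer with either of the first two options, yet the model reads the second as a worse state than the first. Because the outcome is a change between two visits, someone with zero days both times can tick one box at baseline and the other at 6 months and be recorded as improved or worsened. The research nurse's check of the questionnaire (Recruitment; Background measurements) would not flag this, because neither answer is wrong.

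Sick leave features in the aims and in the article's claim to novelty, and this question is its only measure. The overlap matters more the more people have zero days. The sample must be work-capable, and "Acute mental health symptoms and inability to work" is an exclusion criterion, so many zeros are a reasonable expectation. That is an inference; the article does not state it.

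An analysis plan that is not shown could not fully repair this. Once collected, the zeros among the 0–6 answers cannot be told apart from people with one to six days.

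**Working it through.** **1. Overlap check.** Each whole number of days from 0 to 184 (about six months) was compared with the six printed options. Zero fits two of them. Each of 1 to 184 fits exactly one, and there are no gaps. With 1–6 in place of 0–6, every value fits exactly one option.

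**2. The plan's own figures.** None concerns sick leave. The sample size of 125 rests on CES-D: "We expect depressive symptoms to decrease in the intervention group from 14 to 9.9 points", a difference of 14 − 9.9 = 4.1 points. No standard deviation is given, so 125 cannot be reproduced independently, and this point does not depend on it. What is used below is the number of completers: 125 × (1 − 0.25) = 93.75, about 94, or 47 per arm.

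**3. Share of the second category that are true zeros.** All inputs are assumed. Let p0 be the share with zero days, p1 the share with one to six days, and q the share of zero-day people who tick 0–6. The share is p0·q / (p0·q + p1). With p0 = 0.80 and p1 = 0.12:

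| q | Calculation | True zeros in the 0–6 box |
|---|---|---|
| 0 | 0 / 0.12 | 0% |
| 5% | 0.04 / 0.16 | 25% |
| 10% | 0.08 / 0.20 | 40% |
| 25% | 0.20 / 0.32 | 62.5% |

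The result also depends on p0. Holding q at 10% and setting p1 to 60% of the non-zero remainder, p0 = 70%, 80%, 90% and 95% give 28%, 40%, 60% and 76%.

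**4. Apparent change without real change.** For a person with zero days at both visits, if the two choices are independent, the chance of ticking different boxes is 2q(1 − q): 9.5% at q = 5%, 18% at 10%, 37.5% at 25%. People who answer consistently would show less.

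**5. Mis-ticking at the same rate in both arms.** Simplify to any versus no leave, with assumed true rates of 20% and 5% and 47 per arm. Observed rates become 0.20 + 0.80q and 0.05 + 0.95q, so the difference is 0.15(1 − q). Two-sided 5% power by normal approximation:

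| q | Observed rates | Difference | Power |
|---|---|---|---|
| 0 | 20.0% v 5.0% | 15.0 points | 0.60 |
| 5% | 24.0% v 9.75% | 14.25 points | 0.45 |
| 10% | 28.0% v 14.5% | 13.5 points | 0.36 |
| 25% | 40.0% v 28.75% | 11.25 points | 0.21 |

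The difference shrinks and power falls. With no true difference, equal q in both arms produces none.

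**6. What a false difference would need.** Suppose 85% have zero days in both arms. If q were 10% in one arm and 5% in the other, the apparent gap in any leave would be 0.85 × (0.10 − 0.05) = 4.25 points. It is zero when q is equal. The article gives no basis for unequal rates.

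**7. Cost of merging the two lowest levels.** If 85% have zero days and 10% have one to six, the merged level holds 95%, leaving 0.05 × 94 = 4.7, about 5 completers across the four upper levels. With 80% and 12% it holds 92%, leaving 0.08 × 94 = 7.5.

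**The case against.** The strongest reply is that the overlap may do nothing. 'No days' is offered first and matches a zero-day respondent exactly; beside it, 0–6 reads naturally as some days, up to six. If everyone reads it so, q = 0 and there is no effect. This stands: the article shows that misrecording is possible, not that it happens.

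The printed options may also be a slip. Participants need adequate Finnish and the questionnaire is not shown, so the survey itself may read 1–6. That stands as a possibility, but something still needs correcting: the article in that case, the survey otherwise.

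A reader might go further and infer that the outcome is in fact misclassified at its commonest value, or that counselled participants will drift towards 'No days' and produce a spurious benefit. The documents support neither. No distribution is given, and a spurious benefit requires mis-ticking that differs by arm. The article's Summary does concede that participants are unblinded and that expectancies may influence self-report, but that general limitation would remain with a 1–6 option too.

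Finally, merging the two lowest levels in the main model could cost more than the defect, as step 7 shows. That stands, and it limits merging to a sensitivity analysis.

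**Conclusion.** The point holds as a defect in the response options as printed: the two lowest overlap at zero, the ordinal analysis separates them, and nothing in the article resolves it. The overlap itself needs no assumption.

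The size of the consequence is unknown. It is nil at q = 0. At assumed mis-ticking of 5% to 25%, it ranges from modest to serious contamination of the second category, and every such figure rests on assumed shares. The expected effect on the group comparison is noise and a diluted difference, not a false one. The outcome is secondary; CES-D, both work-ability indicators and the sample size are untouched. This is a correction worth making, below the level of something that must be fixed for the trial to be sound.

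**What to change.** Check the wording in the live questionnaire.

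- If it already reads 1–6 days, correct the article.
- If it reads 0–6 and no baseline answers have been collected, change the second option to 1–6 days in both the baseline and the 6-month survey. This is a one-character edit.
- If baseline answers were collected with 0–6, keep the wording identical at 6 months so that the two visits remain comparable. Leave the planned ordinal model on the original levels as the main analysis. Before outcome data are seen, specify a sensitivity analysis that merges the two lowest levels.

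The sensitivity analysis needs one recode. Its cost is the lost distinction between no days and one to six days, and possibly very few people above the merged level, so it should be reported with the category counts and read with that in mind.
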